#### Condition 1: Identity Exchange With Exposure to Sexual Harassment

Couples in this experimental group will experience an identity exchange with their partner in a VR environment. In this case, male participants will be exposed to an immersive scene of sexual harassment while they virtually embody the avatars of their female partners.

#### Condition 2: Identity Exchange Without Exposure to Harassment

In this condition, male participants will also virtually embody the avatar of their female partners; however, in this condition, they will go through a neutral scene, not including sexual harassment. It is intended that participants experience the perspective of their partners in a scenario that does not involve gender-based violence.

#### Condition 3: Third-Person Observer

Participants will observe a scene of sexual harassment in a virtual environment, but this time from a third-person perspective since they will embody their own avatar. The purpose will be to assess how observation of harassment affects participants’ attitudes toward sexual harassment and their empathetic responses to the survivor.

### Intervention Description

The REVISE intervention will be delivered using a head-mounted display with integrated eye-tracking and pupillometry capabilities (ie, Tobii VR headset). The virtual environments will be developed using the Unity game engine and implemented through the Tobii SDK for real-time eye-tracking and data acquisition. Avatars will be created through manual customization and synchronized with participants’ real-time body movements to induce a body ownership illusion. This embodied perspective-taking mechanism is expected to influence participants’ interpretations of sexual harassment scenarios and beliefs related to sexual aggression. During the intervention, both partners will wear head-mounted displays and interact in real time from separate physical spaces. The content and narrative structure of the virtual scenes will be identical across conditions, differing only in perspective (ie, first-person vs third-person) and exposure to sexual harassment content, according to experimental allocation.

While the primary intervention targets the male partner’s perspective, female partners play a triadic role: (1) providing ecological validity to the VR interaction through their virtual representation, (2) providing “observer-report” data on relationship functioning and perceived empathy, and (3) acting as prosocial models during the VR scenarios. Specifically, in the harassment exposure condition with identity exchange, female partners are instructed to model empathetic and assertive responses to the simulated harassment. This allows the male partner (now embodied in the female avatar) to experience and internalize a constructive, prosocial reaction to aggression from a first-person perspective. These dyadic data and interactions are essential to triangulate the self-reported changes in men and to assess whether the intervention impacts the couple’s interactional climate.

### Intervention Procedure

The intervention follows 5 phases, as shown in Figure 1. Each participant will arrive at the laboratory and provide their consent to participate in the study. They will be randomly assigned; participants will be naïve to the study hypotheses. While avatar creation takes place, the couple will answer preintervention questionnaires. Phase 1 also involves the process of personification of the avatar according to the condition in which they will be assigned (see the section on the Intervention Description).

During phase 2, the participants will perform a mirror embodiment task to familiarize themselves with the virtual environment and their new virtual body. More specifically, a female virtual assistant will welcome the participants and instruct them to perform some physical body movements while observing themselves in a virtual mirror. The observation of real-time movements in the embodied avatar, which corresponds to the participants’ real body movements, will allow for greater immersion, as well as enhance body ownership and agency toward the virtual body. For assessment purposes, the female assistant will be a sexualized avatar. During this initial outreach, eye-tracking data will be collected from the participants in relation to the assistant’s cleavage, as gaze fixation on sexualized body parts has been identified as a marker of sexual objectification [47,52]. Once the training and embodiment process is completed, participants will be asked the first questions related to embodiment to check the degree of embodiment achieved.

In phase 3, men will have a 180-second adaptation period in which they will be in an empty bar, and nothing will happen, while women will be in a neutral playful setting in all 3 conditions. Condition 1 men will be involved in a situation of sexual harassment by a group of other men (eg, unwanted flirting, verbal intimidation, and sexist comments). In condition 2, they will stay the same length of time as in the other conditions, but in this case, they will not be sexually harassed. Finally, those in condition 3 will witness the same harassment as in condition 1, but from a bystander perspective, that is, the assaulted person will be a random virtual woman. While people are exposed to the scenarios, their emotional arousal will be assessed by pupillometry in the 3 experimental conditions; however, SAM will be used at the end of phase 3.

Phase 4 will be similar for the 3 conditions. In condition 1, men will have a virtual meeting with their partners (both still with the exchanged identity) outside the context in which the harassment situation occurred. The man will be asked to recount his experience related to the harassment experienced virtually to his partner, who will then be asked to respond empathetically. In condition 2, participants will also meet with their partners (maintaining the virtual identity exchange) outside the scenario in which they were and will be asked to discuss their concerns and expectations of the relationship related to gender issues. In condition 3, participants will discuss the sexual harassment they witnessed in the bar scene, while embodying their own avatar (not exchanged). This discussion will emphasize their reflections on the observed behavior and its consequences, promoting personal insights from their perspective as bystanders.

In phase 5, the sexualized female avatar will appear to perform the farewell, and the participants’ gaze will be traced. Before the end, two questions related to body belonging will be asked. Outcome assessments will be conducted immediately after the intervention (posttest) and at 3 months (follow-up).

The intervention will be discontinued for a participant if they experience severe cybersickness (eg, nausea, dizziness, and disorientation), acute psychological distress, or technical failures that compromise the integrity of the experience or data collection. Participants will be informed that they may request to stop the session at any time without providing a reason. In such cases, the session will be immediately terminated, and appropriate support will be offered if needed.

### VR Scenes Development

Although the structure of the scenes has already been designed, they will be tested and validated through focus groups with female survivors of sexual harassment and professionals working with male aggressors. Additionally, the entire tool will be piloted with the 10 couples mentioned above.

### Trial Design

This randomized superiority trial seeks to compare the efficacy of the REVISE intervention in influencing beliefs related to sexual aggression and associated psychosocial mechanisms, including empathy and perspective-taking, among heterosexual men under three conditions: (1) partner identity exchange in a virtual sexual harassment context, (2) partner identity exchange in a neutral context (ie, no sexual violence included), and (3) no identity exchange with observation of sexual violence context. REVISE involves an accessible digital modality that allows for the immersion and experience of the scenarios to which participants will be exposed. The 3-arm design was chosen to disentangle the effects of embodiment from exposure to sexual harassment content. Condition 1 combines first-person embodiment through partner identity exchange with exposure to a sexual harassment scenario. Condition 2 controls for embodiment without harassment exposure. Condition 3 controls for harassment exposure without embodiment, as participants observe the scenario from a third-person perspective. This structure allows identification of whether observed effects on beliefs and attitudes are driven primarily by embodiment, by narrative exposure, or by their combination.

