#### Change in Body Ownership Illusion

To assess body ownership and agency from a first-person perspective, a validated 4-item scale will be administered verbally at two time points during the IVR experience (see Figure 1 and Table 1):

Mirror embodiment phase: The assistant will ask participants to look at a virtual mirror and rate, on a scale from 0 to 10, the extent to which they felt that the virtual body reflected in the mirror was their own. Participants will then look down and respond to the same question regarding their virtual bodies.Farewell phase: At the end of the IVR session, participants will answer two additional questions: “Did you feel that you owned a different body during the experiment?” and “Did you feel fear of aggression at any point in the experiment?” on the same scale (0-10).

**Table 1 table1:** Trial schedule.

Time point	Preintervention	Allocation	Postallocation		
		0	Intervention day	1 week after intervention^a^	3 months follow-up^b^
Enrollment	✓				
Eligibility screen	✓				
Informed consent	✓				
Allocation randomization		✓			
Baseline			✓		
Embodyment task			✓		
IVR^c^ exposure condition 1			✓		
IVR exposure condition 2			✓		
IVR exposure condition 3			✓		
Self-report assessment^d^			✓	✓	✓
Physiological measures (eye-tracking and pupillometry)			✓		
Change interview			✓	✓	✓

^a^The 1-week postintervention evaluation examines short-term retention of intervention effects.

^b^The 3-month follow-up was chosen to assess long-term changes.

^c^IVR: immersive virtual reality.

^d^Self-report assessments include Interpersonal Reactivity Index (IRI), Ambivalent Sexism Inventory (ASI), Communication Patterns Questionnaire (CPQ), Acceptance of Modern Myths About Sexual Aggression (AMMSA) Scale, Dyadic Adjustment Scale (DAS), Couple Flourishing Measure (CFM), Self-Assessment Manikin (SAM), and body ownership.

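### Three arms cannot identify whether effects come from embodiment, exposure or their combination; they support only comparisons of three packages

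*Protocol article*

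**What the plan says.** Trial Design gives the reason for three arms: "The 3-arm design was chosen to disentangle the effects of embodiment from exposure to sexual harassment content". It then describes the arms. Of the first it says: "Condition 1 combines first-person embodiment through partner identity exchange with exposure to a sexual harassment scenario". Of the second it says: "Condition 2 controls for embodiment without harassment exposure". The third is presented as harassment exposure with no embodiment. The section ends with the inference the authors intend to draw: "This structure allows identification of whether observed effects on beliefs and attitudes are driven primarily by embodiment, by narrative exposure, or by their combination". Strengths and Limitations lists the same separation of embodiment from harassment content as the trial's first strength.

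Intervention Description adds, of what the scenes contain and how their story runs, that these "will be identical across conditions, differing only in perspective (ie, first-person vs third-person) and exposure to sexual harassment content". The same section gives the female partners in the harassment-with-exchange arm an instruction to model empathetic and assertive reactions. Intervention Procedure gives each arm its own phase 4 conversation. In condition 2 the couple "will be asked to discuss their concerns and expectations of the relationship related to gender issues". For the scene in condition 3 it says that "the assaulted person will be a random virtual woman". The Condition 3 section says that these men embody their own avatar.

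**The concern.** Describing an effect as due to embodiment, to exposure or to both together treats the arms as cells of a two-by-two layout: identity exchange (yes or no) by harassment (yes or no). The cell with neither is absent, so change that would occur without either component (retesting, novelty of the headset, meeting the partner in virtual reality) is never observed. Baseline scores within each arm do not replace it.

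The arms also differ in ways that change together with exchange or harassment. A difference between two arms could therefore be credited to embodiment when it comes from who was harassed, how the partner responded or what was discussed afterwards. At stake is the mechanistic conclusion, which is the stated reason for having three arms.

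**Working it through.** The plan gives no figure for this claim, so there is none to reproduce. The check is which quantities three arm means can determine.

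**Inputs.** The three arms as defined in Trial Design. Write x = 1 for partner identity exchange, h = 1 for harassment, and model mean change as b0 + E·x + H·h + EH·x·h.

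- C1 (x = 1, h = 1) = b0 + E + H + EH
- C2 (x = 1, h = 0) = b0 + E
- C3 (x = 0, h = 1) = b0 + H
- x = 0, h = 0: mean b0, no such arm

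**Estimability.** The design matrix has rank 3 for 4 parameters. The estimable differences are:

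- C1 − C2 = H + EH
- C1 − C3 = E + EH
- C2 − C3 = E − H

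E, H and EH are each not estimable. In particular EH = C1 − C2 − C3 + b0, and b0 is not observed. With the fourth cell the rank would be 4.

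**Illustration.** The documents give no arm means, so assume changes of −0.8, −0.4 and −0.4 SD in C1, C2 and C3. Then EH = −0.8 + 0.4 + 0.4 + b0 = b0, with E = −0.4 − b0 and H = −0.4 − b0.

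| Assumed b0 | E | H | EH | Reading |
|---|---|---|---|---|
| 0 | −0.4 | −0.4 | 0 | purely additive |
| −0.2 | −0.2 | −0.2 | −0.2 | mixed |
| −0.4 | 0 | 0 | −0.4 | combination only |

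Every row gives the same three arm means, and C1 is 0.4 SD better than each control in every row. The ambiguity does not depend on the values chosen. Changes of −0.4, 0 and 0 fit (b0, E, H, EH) = (0, 0, 0, −0.4) and (0.4, −0.4, −0.4, 0) equally well.

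**What else changes between arms.** From Intervention Description, Intervention Procedure and the condition descriptions:

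| | C1 | C2 | C3 |
|---|---|---|---|
| Avatar | partner's | partner's | own |
| Person harassed | the man, in his partner's avatar | nobody | an unknown virtual woman |
| Stated partner instruction | model empathetic and assertive reactions; answer empathetically in phase 4 | none | none |
| Phase 4 topic | his own virtual harassment | gender-related concerns in the relationship | harassment seen as a bystander |

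So C1 − C3 is E + EH plus victim identity, partner instruction and a different phase 4 task. C1 − C2 is H + EH plus partner instruction and a different phase 4 discussion. C3 involves embodiment of a kind, in the man's own avatar; what it lacks is the exchange.

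**The case against.** The strongest reply is that the text never mentions a factorial interaction. On a looser reading the three arms work as a dismantling design. If C1 and C2 do equally well and beat C3, that points to embodiment. If C1 and C3 do equally well and beat C2, that points to exposure. If C1 beats both, the full package is needed for the best result. The hypothesis (condition 1 against the controls) and the primary model (condition by time) need no fourth cell.

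Much of this stands. The pairwise differences are randomised, the hypothesis is testable and the first two patterns would be informative, subject to the phase 4 differences. But Principal Findings expects the strongest effect in condition 1, and that is the pattern that fits both additive effects and a pure combination effect. The sentence in Trial Design promises more than a ranking of packages.

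A second reply is that the statement of identical scenes concerns scene content and narrative, not the conversations, and that the partner instruction and phase 4 tasks are openly described. That is right. Only the identity of the harassed person clearly conflicts with that statement. Disclosure does not remove the confounding, however.

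A reader might also infer that the protocol contradicts itself on the women's role, since they are in a neutral setting in phase 3 yet are to model reactions to harassment. The documents do not establish this. Intervention Procedure places the partner's empathetic response in phase 4, which fits both statements; at most the phase of the modelling is left unstated.

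**Conclusion.** The point holds for the mechanistic claim only. With three of the four cells present, the separate effects of embodiment and exposure and their interaction cannot be identified. The available contrasts also mix in partner instruction and phase 4 content, and condition 1 versus 3 mixes in victim identity. The estimability result needs no numerical assumption; the SD values above are illustrative.

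A reader might go further and say that no result of this trial could support any conclusion. The documents do not support that: comparisons of condition 1 with each control as whole packages are valid, and the design is partly informative about mechanism.

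A reader might also bring in the body-ownership items, because the farewell questions differ from the mirror questions and one asks "Did you feel fear of aggression at any point in the experiment". That is a separate oddity. No section relies on those items to settle attribution, so they neither support nor weaken this point.

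**What to change.** Replace the closing sentence of Trial Design, and the matching strength in Strengths and Limitations, with a statement of this content:

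- Condition 1 versus condition 2 estimates the effect of adding the harassment scene with its phase 4 conversation, given identity exchange.
- Condition 1 versus condition 3 estimates the effect of the identity-exchange package compared with bystander viewing in one's own avatar.
- The interaction and the separate main effects are not identifiable.

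In Trial Design, describe condition 3 as lacking partner identity exchange. In Intervention Description, state that victim identity, partner instruction and phase 4 task also differ by arm, and say in which phase the modelling takes place.

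The cost is text in a few places and a narrower mechanistic claim. Arms, sample size and primary model stay as they are, and the Results section says recruitment had not begun as of January 2026.

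A fourth arm would make the interaction estimable but would be a poor remedy at this size. With 30 couples per cell, unit SD and two-sided α of .05, the standard error is √(4/30) = 0.365. Power for an interaction of 0.4 SD is then Φ(0.4/0.365 − 1.96), about 19%, and for 0.8 SD about 59%. Giving all arms the same phase 4 instruction would alter the intervention itself and is not needed for this correction.

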### Data Analysis Plan

All statistical analyses will be performed using R (R Core Team) with relevant packages including *lme4*, *nlme*, *geepack*, and *mice* [54].

#### Quantitative Analysis

##### Primary Analysis

The primary outcome is the change in beliefs related to sexual aggression. The primary comparison of interest is the condition × time interaction—specifically, whether change from baseline to postintervention and from baseline to 3-month follow-up differs across the 3 experimental conditions (IVR-based intervention, control condition A, and control condition B). This will be estimated using a single prespecified linear mixed-effects model with fixed effects for condition (3 levels, dummy-coded), time (3 levels, with baseline as reference), and their interaction, and random intercepts for couples and for participants nested within couples. The female partner’s scores (eg, Dyadic Adjustment Scale and Couple Flourishing Measure) will be included as covariates to control for baseline relationship quality. This model structure was selected as the primary analytic approach; ANOVA-based omnibus tests and simpler regression models will not serve as primary analyses but may be reported descriptively.

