## Methods

### Objectives

The primary objective of this randomized controlled trial is to evaluate the efficacy of the REVISE intervention in reducing beliefs that legitimize or minimize sexual aggression (Acceptance of Modern Myths About Sexual Aggression [AMMSA] scale) among heterosexual men at postintervention and at 3-month follow-up.

The secondary objectives are

To evaluate the effects of the REVISE intervention on empathy, gender role attitudes, relationship functioning, and communication patterns.To assess changes in physiological responses (eye tracking and pupillometry) during the IVR experience across experimental conditions.To explore participants’ subjective experiences and perceived changes following the intervention through qualitative interviews, and to integrate these findings with quantitative outcomes.

It is hypothesized that participants exposed to identity-swapping with sexual harassment scenarios will show greater reductions in beliefs legitimizing sexual aggression compared to the control conditions.

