This study is designed as a randomized, parallel-group, superiority trial with 3 arms and a 1:1:1 allocation ratio. An a priori power analysis was conducted to determine the necessary sample size to detect a meaningful effect in the primary outcome measure. Considering the study design, an estimated effect size of *d*=0.4, statistical power of 0.9, and α level of .05, the required sample size was calculated to be 84 heterosexual couples. To account for potential attrition (estimated at 7%), a total of 90 couples will be recruited. While the a priori power calculation was based on a standard framework, the final sample (N=180 individuals; 90 units of randomization and 30 couples per experimental condition) was increased to provide additional robustness for the planned longitudinal and dyadic analyses. The sample size estimation was based on a conservative effect size derived from prior studies. Although the calculation does not explicitly model the multilevel structure of the data (ie, repeated measures nested within individuals and couples), the use of mixed-effects models in the analysis phase is expected to appropriately account for this dependency structure. The allocation sequence will be computer-generated using random block sizes of 3 or 6 by a research assistant not involved in recruitment, assessment, or intervention delivery. Allocation will be concealed until participant enrollment and completion of baseline assessments (see Figure 1).

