## Results

As of January 2026, the trial has not started recruiting participants. Ethical approval has been obtained (approval code CE23-PF02), and the intervention materials and procedures are finalized for implementation. Recruitment and data collection are planned from March 2026 to March 2027, with primary endpoint assessments conducted immediately postintervention and at 3-month follow-up. The first results are expected after completion of follow-up assessments.

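### The primary comparison is a non-directional three-arm, two-time interaction, which does not test the stated hypothesis that condition 1 beats the controls, and no success rule is fixed

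*Protocol article*

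**What the plan says.** The Objectives state a directional hypothesis: participants given identity exchange with harassment "will show greater reductions in beliefs legitimizing sexual aggression compared to the control conditions". That amounts to condition 1 against condition 2 and condition 1 against condition 3.

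The Primary Analysis section fixes something else. "The primary comparison of interest is the condition × time interaction", it says, and explains this as "whether change from baseline to postintervention and from baseline to 3-month follow-up differs across the 3 experimental conditions". The model has "fixed effects for condition (3 levels, dummy-coded), time (3 levels, with baseline as reference), and their interaction". A reference level is given for time but none for condition. The section adds that "ANOVA-based omnibus tests and simpler regression models will not serve as primary analyses but may be reported descriptively".

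Both post-baseline times have equal standing. The Objectives name both, and the Results section speaks of "primary endpoint assessments conducted immediately postintervention and at 3-month follow-up".

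**The concern.** A difference among three arms is not the same as condition 1 being better than its controls. The interaction can be significant because the two controls differ from each other, or because a control outperforms condition 1.

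These are the cases the design is meant to separate. The Trial Design section says the three arms should show whether effects come from embodiment, from exposure or from their combination. If embodiment alone acts, conditions 1 and 2 are equal and condition 3 differs. If exposure alone acts, conditions 1 and 3 are equal and condition 2 differs. In either case the primary comparison can be significant although condition 1 does not beat both controls.

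The remark that ANOVA-based omnibus tests are not primary leaves it unclear whether a joint test or individual coefficients decide the trial. A reader of the final report could not tell from this article what a positive primary result means.

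**Working it through.** **Inputs.** From the article: three arms, 30 couples per arm, baseline plus two post-baseline times, α=.05 and "an estimated effect size of *d*=0.4". Assumed: two-sided tests, men's scores only, a random-intercept model with within-person correlation r of .5 to .7, an SD of 1 at each time, and a correlation of .3 to .7 between the estimated effects at the two times. Two contrasts that share condition 1 in equal arms correlate .5.

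**The plan's own figure.** The article gives no error rate to reproduce. Its one related figure is 84 couples for d=0.4 at 90% power. A pairwise contrast needs 2(1.960+1.282)²/0.4² = 131.3, so 132 per arm. A three-group one-way ANOVA F test with Cohen's f=0.4 gives 84 in total (power .907). The stated size therefore matches an omnibus test, and only if d is read as f.

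**Reading A: one joint 4-df interaction test.**
- Under no effect, simulated rejection is 5.0% to 5.2%, so type I error is held.
- Now let conditions 1 and 2 be equal and condition 3 better by δ=0.4 SD at both times. The noncentrality is λ = nδ² × (2/3) × (2/3)/(1−r). The two factors of 2/3 are the sums of squares of the centred arm pattern (0,0,1) and the centred time pattern (0,1,1).
- r=.5: λ = 30×0.16×0.444/0.5 = 4.27. With F on 4 and 174 df, rejection is 33%.
- r=.7: λ = 7.11, and rejection is 53%.
- In simulation, 30% (r=.5) to 49% (r=.7) of trials rejected while no condition 1 contrast showed benefit.
- When both controls beat condition 1 by 0.4 SD, the test again rejects in 33% to 53%.

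**Reading B: four condition 1 coefficients** (two controls × two times), each at two-sided 5%, from 1,000,000 multivariate normal draws under no effect.

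| Correlation between times | At least one significant | At least one false claim of condition 1 benefit |
|---|---|---|
| .3 | 16.9% | 8.5% |
| .5 | 16.2% | 8.1% |
| .7 | 14.9% | 7.4% |

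Four independent tests would give 1 − 0.95⁴ = 18.5%.

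**Reading C: one 2-df omnibus test per time point,** each at 5%. Familywise error is 9.5%, 9.2% and 8.4% at correlations .3, .5 and .7. This reading shares both weaknesses.

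**Power of the contrasts that match the hypothesis,** d=0.4, 30 per arm. The expected z is 0.4/√(2/30) = 1.549.
- At .05: P(Z > 1.960 − 1.549) = 34%. At .025: P(Z > 2.241 − 1.549) = 24%.
- With baseline adjustment, z is divided by √(1−r²), giving 1.789 (r=.5) and 2.169 (r=.7). Power at .05 is 43% and 58%.
- Beating both controls at one time, each at .05: 19% without baseline adjustment, 27% to 42% with it.

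**The case against.** Five points deserve weight.

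**The omnibus reading is an inference.** The section says ANOVA-based omnibus tests are not primary and describes estimation from one dummy-coded model. That can also be read as reporting coefficients. This stands, but it removes one fault only to bring in the other. Asking whether change differs across three conditions remains a non-directional question.

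**The faults belong to different readings.** A reader might infer that the trial has an omnibus primary test with no error control. The documents do not support that: a single joint test holds 5%, and the 15% to 17% arises only if any one of four coefficients counts as success, a rule the article does not state.

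**A both-controls rule would need no adjustment for two comparators.** This is correct. If condition 1 must beat both controls at the same time point, at either time, a false claim occurs in about 0.8% to 0.9% of trials under no effect. It occurs in 4.2% to 4.8% when condition 1 equals one control and far exceeds the other. That exceeds the 2.5% for one direction only because there are two times. The article does not state this rule either.

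**Multiplicity and contrast lists often sit in an analysis plan,** and none is shown. It therefore cannot be said that no procedure exists. What remains does not depend on an omission: the primary comparison is stated here and differs from the hypothesis stated here.

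**Coding.** A reader might infer that a control is the reference level, so that one condition 1 comparison is not a coefficient. No reference level for condition is given, and under any coding each comparison is a linear contrast of the same fitted model.

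**Conclusion.** The point holds as a mismatch and an unfixed decision rule. The primary comparison as defined can be positive when condition 1 beats neither control: in about a third to a half of trials, for a 0.4 SD difference confined to condition 3. If it is read instead as separate condition 1 coefficients, it addresses the hypothesis but carries a familywise error of about 15% to 17%, with a false claim of benefit in about 7% to 8.5%.

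The rejection rates depend on the assumed within-person correlation and on the random-intercept model. The error rates depend on the assumed correlation between times. Two-sided testing is assumed throughout. The mismatch between the Objectives and the Primary Analysis section depends on none of these. It should be corrected before data are seen. The article reports that recruitment had not begun as of January 2026.

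**What to change.** Keep the mixed model and change what is read from it.

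1. Define the primary estimands as the contrasts in AMMSA change, condition 1 minus condition 2 and condition 1 minus condition 3.
2. State the success rule. If condition 1 must beat both controls, test each at two-sided 5% with no adjustment for two controls. If beating either is enough, use Holm.
3. Handle the two time points by a fixed testing order or another stated adjustment. Both can then stay in the primary objective. Giving one time point secondary status is possible but not required, and is the sponsor's choice.
4. Report the joint interaction and condition 2 minus condition 3 as secondary. They still serve the aim of separating embodiment from exposure.

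The cost in work is wording only. The statistical cost is lower power per contrast: about 34% at .05, or 24% at a first Holm step of .025, for d=0.4 with 30 per arm and no baseline adjustment. With baseline adjustment at r=.5 to .7 it is 43% to 58% at .05. The joint test is no stronger protection, since it rejects in only about 33% to 53% of trials when condition 1 is truly better by that amount.
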